### Sample size calculations

To account for cluster randomisation, sample size calculations were based on recent sample size requirements developed by Heo & Leon [49]. to detect intervention by time interactions in longitudinal cluster randomised clinical trials. The CSC trial will be powered to detect differences in the overall sample as well as between samples from each of four groups within the three States of NSW, QLD and WA. To allow for comparisons within each State, six schools (with at least 100 students) in each of the four intervention groups are required per state, giving a total of 24 schools per State (at least 2400 students). This achieves 80 per cent power to detect a standardized between-group mean difference of 0.15 (p = 0.05) in outcomes at the end of the trial with seven measurement occasions. An effect size of 0.15 is comparable to previous school-based trials of universal mental health and substance use prevention programs and would have substantial benefits on a population level based on recent economic modelling [50]. To account for school dropouts during the trial, which we expect to be approximately 10 per cent, we aim to recruit at least 28 schools in each State (at least 2800 students). This will result in an overall sample of 8400 students from 84 schools at baseline to test the efficacy of the CSC intervention in comparison to the other groups. Based on previous research using the *CLIMATE Schools* programs, school participation rates for similar trials were approximately 30 per cent [48,51]. Therefore, to recruit a total of 84 schools, approximately 270 schools will be approached to participate.

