#### ***Statistical analysis***

Single-level analyses; one-way analyses of variance (for normally distributed data), Chi-square (for binominal data), and Mann-Whitney U-test (for non-normally distributed data) will be used to examine baseline equivalence and attrition between groups. Due to the multi-level and hierarchical nature of the data, mixed effects regression will be used to examine intervention by time interaction effects. To account for intracluster variance within States or schools, intervention effects will primarily be examined using hierarchical linear modelling (HLM) for normally distributed data and hierarchical generalized linear modelling using a Poisson distribution for count data. Outcome variables will be centred at post-test to allow for comparisons between groups immediately after the intervention, and growth terms will be analysed to determine the magnitude of the follow-up effects. Analyses will be conducted using the program Stata. If unconditional models reveal that less than 10% of systematic variance exists at the between State or between school level for any outcome variable, HLM will be abandoned and single-level analyses will be used [67]. For these variables, ANCOVAs utilising the SPSS GLM procedure will be conducted to account for any baseline differences that might exist between groups. For multiple comparisons Bonferroni adjustments will be made. Effect sizes, odds ratios and 95% confidence intervals will also be calculated.

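### The post-test contrast in the primary hierarchical models has no stated adjustment for the Survey 1 score, and it sits in the branch where chance differences between schools are largest

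*Protocol article*

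**What the plan says.** The Statistical analysis section of the Protocol article describes two branches.

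- **Primary branch.** The section states that "intervention effects will primarily be examined using hierarchical linear modelling (HLM) for normally distributed data", with a hierarchical Poisson model for counts. Two readouts are named: the level at post-test ("Outcome variables will be centred at post-test to allow for comparisons between groups immediately after the intervention") and the later course ("growth terms will be analysed to determine the magnitude of the follow-up effects"). The same section says that "mixed effects regression will be used to examine intervention by time interaction effects". No baseline covariate or baseline constraint is named for these models.
- **Fallback branch.** If an unconditional model puts less than 10% of the variance at State or school level, "HLM will be abandoned and single-level analyses will be used". For those outcomes, "ANCOVAs utilising the SPSS GLM procedure will be conducted to account for any baseline differences that might exist between groups".

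The section Sample size calculations bases the trial on an intervention-by-time interaction over seven occasions. Its target is a "standardized between-group mean difference of 0.15 (p = 0.05) in outcomes at the end of the trial", with six schools of at least 100 students per arm in each State. Under Assessment occasions, Survey 1 is the baseline and is taken by all students.

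**The concern.** In a growth model, moving the time origin to post-test makes the group coefficient the fitted difference in level at that time. If Survey 1 is simply one of the repeated outcomes and each arm has its own starting level, a baseline gap between arms is not subtracted from this coefficient. A lasting gap passes into it in full.

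The article recognises that arms may start apart, but ties the remedy to the ANCOVA branch. The 10% rule sends outcomes with little clustering to ANCOVA and keeps those with strong clustering in the hierarchical model. The stated adjustment is therefore present where school differences are small and absent where they are large. At stake are the precision of the post-test contrast and its exposure to chance imbalance. This matters most within a State, where the article plans comparisons on about six schools per arm.

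**Working it through.** **Inputs from the article.** Target 0.15 SD; 80% power; alpha 0.05 (two-sided assumed); 100 students per school; 6 schools per arm per State after dropout, so 18 per arm over three States; 28 schools per State recruited, so 7 per arm, and 84/4 = 21 per arm overall if allocation is equal.

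**Assumptions, because the article gives no values.** School-level ICC 0.10, the point at which the hierarchical model is kept if all clustering is between schools; baseline to follow-up correlations rb between schools and rw within schools; normal approximations; a continuous outcome.

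**1. Which contrast does the stated 80% belong to?** Take a random-intercept slope formula with seven equally spaced occasions (variance of time 4) and a difference of 0.15/6 = 0.025 per occasion:

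schools per arm = 2(1 − ρ)(1.96 + 0.84)² / (100 × 7 × 4 × 0.025²) ≈ 8.97(1 − ρ)

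Here ρ is the within-student correlation, which is not stated. The result is 6.28 at ρ = 0.30, 6.01 at 0.33 and 5.83 at 0.35. Power with 6 schools is 78.2%, 79.9% and 81.1%. So the stated figure is compatible with an interaction test at ρ of about 0.30 to 0.35, but cannot be confirmed. A plain post-test comparison of 600 students per arm reaches only 74% even at ICC 0. The power statement therefore belongs to the interaction.

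**2. Does a baseline gap reach each readout?** Fit a straight line at approximate survey months 0, 6, 12, 13, 18, 24 and 30, read from the term timeline (mean 14.71, sum of squares 633.4).

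- *Level at post-test.* The weights are 1/7 + (c − 14.71)(t − 14.71)/633.4, where c is the centring month. They sum to 1, so a lasting school difference passes in full. Survey 1 itself has weight +0.345 when centring at Survey 2 and +0.183 at Survey 4, so it is added, not subtracted.
- *Slope.* The weights sum to 0, so a lasting difference cancels.

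With ρ = 0.5 and 6 schools per arm, the variance of the level contrast is (2/6)[ICC + (0.5 − ICC)/100 + 0.5·Σw²/100]. Its SE is 0.187 at ICC 0.10. The slope contrast over 30 months has SE 0.049 at ICC 0.02, 0.05 and 0.10 alike.

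**3. Chance imbalance at baseline.** The variance of a school mean is 0.10 + 0.90/100 = 0.109. SE of the difference = √(2 × 0.109/k) for k schools per arm.

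| Schools per arm | SE | P(gap > 0.15 SD) |
|---|---|---|
| 6 (State, after dropout) | 0.191 | 43% |
| 7 (State, recruited) | 0.176 | 40% |
| 18 (all, after dropout) | 0.110 | 17% |
| 21 (all, recruited) | 0.102 | 14% |

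**4. Gain from adjustment.** Adjusted variance = ICC(1 − rb²) + (1 − ICC)(1 − rw²)/100.

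- rb = 0.7, rw = 0.5: 0.10 × 0.51 + 0.90 × 0.75/100 = 0.05775. The cut is 1 − 0.05775/0.109 = 47%. SE falls from 0.191 to 0.139 (k = 6) and from 0.102 to 0.074 (k = 21).
- rb = rw = 0.5: the cut is 25%. SE falls to 0.165 and 0.088.

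This is a single-time-point formula. Its unadjusted SE of 0.191 is close to the 0.187 from the growth model in step 2.

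**5. Sensitivity to the ICC.** If part of the 10% lies between States, it largely drops out of arm contrasts balanced within State, and the school ICC is smaller. At a school ICC of 0.05 the SE is 0.141 with a 29% chance (k = 6), or 0.075 with 5% (k = 21).

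**The case against.** The strongest objection is that the article's stated main test is the intervention-by-time interaction, and the trial is powered on it. If Survey 1 is a modelled occasion, that test compares change and lasting school differences cancel, as step 2 shows. This stands, and it confines the point to the post-test contrast. A reader might infer that the whole primary analysis ignores baseline, or that the 80% power is wrong; the article supports neither.

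Second, the article does not say that baseline covariates are excluded. Modelling later surveys with Survey 1 as a covariate is compatible with its wording, and such detail is often left to an analysis plan. This stands in part: exclusion cannot be inferred. But the section describes both branches and assigns baseline adjustment to one of them, which is more than leaving the matter open.

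Third, an ICC of 0.02 or 0.05, read as school-level variance, would send the outcome to ANCOVA, where baseline is accounted for. This is correct and is why the main figures use 0.10. The same rule makes the remaining branch the more exposed one.

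Fourth, the coefficient at the centring point is a fitted value pooled over surveys, not a raw difference in means. That is correct for a growth model, but the pooling does not remove a lasting gap.

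Fifth, under randomisation the unadjusted contrast is unbiased and its SE already reflects chance imbalance. That is also correct. A reader might infer systematic bias; nothing in the article supports that.

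**Conclusion.** The point holds for the post-test contrast of the hierarchical linear and Poisson models. As written, baseline adjustment is stated only for the fallback, and the 10% rule leaves it unstated where clustering is strongest. The cost is lost precision and exposure to chance imbalance, mainly within State; with about 21 schools per arm overall the exposure is smaller but not negligible. The interaction test is largely protected, provided Survey 1 is among the modelled occasions and school differences are stable over time.

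The sizes in the working rest on the assumed ICC and correlations, neither of which the article gives, and they describe continuous outcomes. With t-based inference on six schools per arm they would be somewhat less favourable. The change is worth making because it uses data already planned for collection.

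**What to change.** State in the analysis section how Survey 1 enters both the HLM and the hierarchical Poisson model, using one of two forms:

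- keep Survey 1 as an outcome occasion and constrain the arms to be equal there; or
- model Surveys 2 to 7 with the student's own Survey 1 score and the school-mean Survey 1 score as covariates.

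Take the post-test and follow-up contrasts from that model, and say whether the post-test level or the interaction is the primary test. The constraint relies on the arms being comparable at Survey 1. School randomisation supports this as long as student consent does not depend on arm. The covariate form does not impose equality, but students without a Survey 1 score need handling.

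The cost is analysis wording only. Survey 1 is already planned for all students, and no visits, schools or students are added. The school-mean covariate uses one school-level degree of freedom: within a State, 24 schools less 4 arms leaves 20, which becomes 19.

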### Objectives of the CSC study

The primary objective of the CSC Study is to evaluate an innovative Internet-based prevention program for the prevention and reduction of substance use, anxiety and depressive symptoms, by combining the universal *CLIMATE Schools - Substance Use* program and the *CLIMATE Schools - Mental Health* program.

It is hypothesised that the CSC program will be more effective than; (1) school-based Health and Physical Education as usual, (2) the *CLIMATE Schools - Substance Use* program, and (3) the *CLIMATE Schools - Mental Health* program in relation to the following outcomes:

1) reducing the use and harmful use of alcohol and cannabis

2) reducing overall levels of anxiety and depression

3) increasing knowledge related to alcohol, cannabis anxiety and depression.

Secondary aims include examining the effects of the interventions on alcohol use related harms, self-efficacy to resist peer pressure, general disability, and truancy. The link between personality and substance use, as well as mental health will also be examined.

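### The growth terms that are to size the follow-up effects measure how fast the group difference changes, not how large it is at follow-up

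*Protocol article*

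**What the plan says.** The Statistical analysis section of the protocol article says that "mixed effects regression will be used to examine intervention by time interaction effects". It fixes the time origin: "Outcome variables will be centred at post-test to allow for comparisons between groups immediately after the intervention". The same sentence then gives the later effects to another parameter: "growth terms will be analysed to determine the magnitude of the follow-up effects". No model-based group contrast at a follow-up survey is named. The section does not say whether growth covers only the surveys from post-test onward or all seven, or whether it is linear, quadratic or piecewise.

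Under Sample size calculations the target is a "standardized between-group mean difference of 0.15 (p = 0.05) in outcomes at the end of the trial with seven measurement occasions", obtained from a method "to detect intervention by time interactions in longitudinal cluster randomised clinical trials". Among the hypotheses under Objectives of the CSC study is "reducing overall levels of anxiety and depression", which is a statement about levels.

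**The concern.** With time zero at post-test, the group coefficient is the gap at post-test and the group-by-growth coefficient is the change in that gap per unit time. The null hypothesis for growth is that the gap stays constant, not that there is no gap at follow-up. The two agree only if the gap is zero at the origin and opens steadily from there. The sample size method can rely on that pattern, because it starts from randomised groups at baseline. Once the origin is moved to post-test, where an effect is already hoped for, the agreement is lost.

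At stake is the answer on lasting benefit. Taken alone, the growth term can miss a benefit that is kept in full, can be significant for one that has vanished, and cannot distinguish a fade that ends at the design effect from a fade that ends at nothing.

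**Working it through.** **Inputs from the article.** Difference 0.15 SD, 80% power, alpha 0.05 and seven occasions. "six schools (with at least 100 students) in each of the four intervention groups are required per state" gives 6 × 100 = 600 students per arm per State, or 1,800 over three States. Follow-ups are at 18, 24 and 30 months.

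**Assumptions.** Two-sided test, SD 1, complete data, random intercepts and no random slopes. Surveys 1 to 3 are at months 0, 6 and 12 (from the school terms in Table 2). Survey 4 is at month 14, since it shares a term with Survey 3; month 13.5 hardly changes the results. The within-student correlation rho is not given. Positive values favour the intervention.

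**1. The plan's own figure.** SE of the slope difference = sqrt(2(1 − rho)/(n × Sxx)). For all seven surveys, mean time = 104/7 = 14.86 and Sxx = 630.9. With rho = 0.4, SE = sqrt(1.2/(600 × 630.9)) = 0.00178 per month. A gap opening linearly to 0.15 has slope 0.15/30 = 0.005, so z = 2.81 and power = 80.2%. Over rho 0.2 to 0.7 power runs from about 68% to 98%. The stated 80% is plausible, but cannot be confirmed without rho. I keep rho = 0.4 because it matches the plan.

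**2. The quantity wanted.** For a straight-line course, the gap at time t after post-test = d + g × t, where d is the post-test difference and g the group-by-growth term. The term g × t equals the gap only when d = 0.

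**3. Reading A: growth over Surveys 2 to 7.** Sxx = 373.3 and SE = sqrt(1.2/(600 × 373.3)) = 0.00231. A fade of 0.15 over 24 months gives g = −0.00625 and z = −2.70.

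| Gap from Survey 2 to Survey 7 | True gap, month 30 | g × 24 | d + g × 24 | P(growth term significant) |
|---|---|---|---|---|
| 0.15 sustained | 0.15 | 0 | 0.15 | 5% |
| 0.30 fading to 0.15 | 0.15 | −0.15 | 0.15 | 77%, control's favour |
| 0.15 fading to 0 | 0 | −0.15 | 0 | 77%, control's favour |

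For rho 0.33 to 0.6 the 77% becomes 72% to 91%. With 1,800 per arm it exceeds 99%, while the sustained case stays at 5%.

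**4. Reading B: one straight line through all seven surveys.** Here g = sum((t − tbar) × gap(t))/Sxx.

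| Gap from Survey 2 to Survey 7 | True gap, month 30 | g × 24 | Fitted gap, month 30 | P(growth term significant) |
|---|---|---|---|---|
| 0.15 sustained | 0.15 | +0.085 | 0.182 | 51% |
| 0.30 fading to 0.15 | 0.15 | +0.041 | 0.222 | 16% |
| 0.15 fading to 0 | 0 | −0.044 | 0.040 | 18% |

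In the sustained case z = 0.00353/0.00178 = 1.98, and the line gives 0.097 at Survey 2 where the truth is 0.15. With rho 0.5 to 0.6 its power is 58% to 68%, against 87% to 93% for linear divergence. With 1,800 per arm at rho 0.4 it is 93%.

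The loss of power depends on when the benefit starts. For a 0.15 benefit starting at Survey 4 (month 13.5) and kept, per-State power is 91% to 97% for rho 0.33 to 0.5. Growth × 16.5 months is then 0.103 and the fitted month-30 gap 0.181, so neither equals 0.150.

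**5. Simulation check.** With 4,000 runs, six schools of 100 per arm, between-school ICC 0.05 and rho 0.5, a benefit sustained from Survey 2 was significant in 58.3% (all seven surveys) and 5.4% (Surveys 2 to 7). A fade to zero over Surveys 2 to 7 was significant in 84.8%.

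**The case against.** A reader might infer that under this plan every sustained benefit will test as no follow-up effect and every fading one as reversed. The article does not support that. It never restricts growth to the post-test surveys, and its sample size rests on an interaction over seven occasions. On that reading a sustained benefit has a favourable slope, the fade from 0.30 to 0.15 is not reversed, and a fade to zero starting at Survey 2 tests as significant only about 18% of the time.

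A reader might also infer that the lasting effect is lost. It is not: the same sentence provides the post-test contrast, and post-test gap plus later change gives the gap at any time. A benefit at post-test with flat growth is ordinarily read as maintained, and the section also promises effect sizes and 95% confidence intervals.

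Four further limits stand. The article does not say that growth is linear. Outcomes with under 10% of variance between schools or States leave the mixed model for ANCOVA, and the simulated ICC of 0.05 would fall there. The earlier trial of the substance use program supports several patterns: weekly alcohol consumption was lower at 6 and 12 months, drinking to excess at 12 months only, and cannabis frequency at 6 months only. And 51% against 80% compares two trajectories, not two analyses of one.

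What does not stand is that this is only detail for the analysis plan. The article makes a positive assignment of the follow-up magnitude to the growth terms, and on neither reading do they measure it.

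**Conclusion.** The concern holds in a limited form. The article names the wrong parameter for the size of the follow-up effects: a growth term is a rate of change in the gap and does not estimate the end-of-trial mean difference that the trial is sized to detect. The null-or-reversed consequence is exact only if growth describes the post-test course (5% rejection for a sustained benefit; about 77% per State in the control group's favour for a 0.15 SD fade). With one line through all seven surveys the consequence is milder: about 51% power per State for a 0.15 SD benefit held from Survey 2, and a slope that still differs from the final gap. The percentages rest on an assumed rho of 0.4, 600 per arm, complete data, no random slopes and a straight-line course. That growth alone is not the follow-up gap needs none of these. The point covers only outcomes that stay in the mixed model. It should be corrected, because the correction is nearly free and decides how lasting benefit is reported.

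**What to change.** Replace the clause on growth terms with wording such as: *For outcomes analysed by the mixed model, follow-up effects are the model-estimated between-group differences, with 95% confidence intervals, at Surveys 5, 6 and 7, calculated as the post-test difference plus the growth terms evaluated at the elapsed time. Growth terms alone will be used only to describe whether the difference widens or fades.* State also which surveys the growth terms cover and their form, because a contrast is only as good as the fitted curve (0.182 instead of 0.150 above). Treating survey occasion as a factor with group-by-occasion terms avoids that dependence and is an optional alternative.

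The cost is a sentence and a few post-estimation contrasts in Stata, with no new data. There is a price in precision: a contrast at a single survey is less precise than a slope if the gap truly diverges linearly, and it carries school-level variance. For a plain comparison at one survey without baseline, with design effect 1 + 99 × ICC, power for 0.15 SD per State is 74% at ICC 0 and 45% at ICC 0.01; over all States it is 99% and 89%. At ICC 0.10 it is 12% and 28%. Taking the contrast relative to Survey 1 removes any school effect that is constant over time. At rho 0.4, SE = sqrt(4 × 0.6/600) = 0.063 and z = 2.37, so power is about 66% per State, against 80% for the slope under linear divergence.

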### Study design

To establish the effectiveness of the integrated CSC intervention, a cluster RCT will be conducted in 84 Australian secondary schools between 2014 and 2016. Cluster randomisation will be employed to avoid contamination of the control group with the intervention group through student communication. Participating schools will be randomly allocated to one of four groups; (1) the *CLIMATE Schools - Combined* condition (CSC), (2) the *CLIMATE Schools* - *Substance Use* condition (CS-SU), (3) the *CLIMATE Schools - Mental Health* condition (CS-MH), or (4) the Control condition (CO). See Table 1 for a graphical display of the experimental design.

**Table 1 T1:** Experimental design

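### The rule that replaces multilevel models with single-level ANCOVA when under 10% of variance lies between States or schools ignores the unit of randomisation, and at about 100 students per school such clustering is not negligible

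*Protocol article*

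**What the plan says.** Under Study design, the article allocates whole schools to four groups: "Cluster randomisation will be employed to avoid contamination of the control group with the intervention group through student communication". Sample size calculations is framed around cluster randomisation and sets the size of the design: "six schools (with at least 100 students) in each of the four intervention groups are required per state", and overall "This will result in an overall sample of 8400 students from 84 schools at baseline".

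Statistical analysis makes hierarchical modelling the primary approach, to allow for variance within States or schools. It then sets a condition: "If unconditional models reveal that less than 10% of systematic variance exists at the between State or between school level for any outcome variable". The consequence when that condition is met is stated just as plainly: "HLM will be abandoned and single-level analyses will be used". For those outcomes the replacement is ANCOVA in SPSS GLM, adjusting for baseline differences between groups. The article keeps no school term, cluster-robust variance or design-effect correction in that fallback. Bonferroni adjustment is promised for multiple comparisons, without their number. No ICC is given anywhere.

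**The concern.** Because the school is the unit of allocation, school-to-school variation is part of the error of every comparison between arms, however small it is. A single-level test leaves it out and so understates the standard error. The understatement grows with the number of students per school, so a cut-off on the variance share alone cannot show that clustering is harmless. A share of 10% might matter little with very small clusters. It matters a great deal with 100 students each.

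The rule may be applied to any outcome, including the primary ones. Where it fires, p-values are too small and confidence intervals too narrow, and chance differences between schools can be read as programme effects. It also contradicts the article's own sample-size reasoning, which treats clustering as something that must be allowed for.

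The trigger is unclear as well. It names State level or school level. Read literally, low variance between the three States could by itself drop the school effect, even where school variance exceeds 10%.

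**Working it through.** **Inputs from the article.** Unit of randomisation: school. Students per school: at least 100. Schools: six per arm per State as required, 84 in total. Level: 0.05 (sidedness not stated, two-sided assumed).

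**Assumed, because the article is silent.** ICC from 0.001 to just under 0.10. The article's term systematic variance is read as the share of total variance, that is, the ICC. m = 100, with m = 50 as a sensitivity check.

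**The article's own figures.**
- Schools: 6 × 4 = 24 per State. For the 10% dropout, 24/0.9 = 26.7, raised to the next multiple of four = 28. Then 28 × 3 = 84 schools, and 84 × 100 = 8400 students. These reproduce.
- Power: "This achieves 80 per cent power to detect a standardized between-group mean difference of 0.15 (p = 0.05) in outcomes". A single comparison of 600 v 600 with no clustering gives 0.15/√(2/600) = 2.598 and power Φ(2.598 − 1.96) = 73.8%. At ICC 0.01 it gives 2.598/√1.99 = 1.842 and power 45%. A random-intercept slope test over seven equally spaced occasions, with within-student correlation 0.33, has a slope difference of 0.15/6 = 0.025 and SE √(2 × 0.67/(600 × 28)) = 0.00893. That gives 2.80 and power about 80%. The correlations used are not stated, so the 80% can be neither confirmed nor refuted. The point here does not depend on it.

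**Error rate of a single-level test.**

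DEFF = 1 + (m − 1) × ICC

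Type I error = 2 × [1 − Φ(1.96/√DEFF)]

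Example, m = 100, ICC 0.01: DEFF = 1 + 99 × 0.01 = 1.99; 1.96/√1.99 = 1.389; error = 16.5%.

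Just under the cut-off (ICC 0.0999): DEFF = 10.89; 1.96/√10.89 = 0.594; error = 55.3%. The confidence interval is too narrow by √10.89 = 3.3.

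| Assumed ICC | DEFF, m = 100 | Unadjusted test, m = 100 (multiple of 5%) | Simulated baseline ANCOVA, m = 100 | Unadjusted test, m = 50 |
|---|---|---|---|---|
| 0.001 | 1.10 | 6.2% (1.2×) | not run | 5.6% |
| 0.005 | 1.50 | 10.9% (2.2×) | 8–11% | 7.9% |
| 0.01 | 1.99 | 16.5% (3.3×) | 11–15% | 10.8% |
| 0.02 | 2.98 | 25.6% (5.1×) | 19–24% | 16.4% |
| 0.05 | 5.95 | 42.2% (8.4×) | 34–43% | 29.1% |
| 0.09 | 9.91 | 53% (10.7×) | 43–54% | 39.9% |
| 0.0999 | 10.89 | 55.3% (11.1×) | not run | 42.0% |

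**Does baseline adjustment cure it?** The simulations assume a student-level baseline–outcome correlation of 0.5 and a school-level correlation r of 0.5 or 0.8. With an adjustment slope near 0.5, residual school variance is about ICC × (1 + 0.25 − r), against a residual total of about 0.75. At r = 0.5 the residual ICC is 0.75/0.75 = 1.0 times the original, so nothing is gained. At r = 0.8 it is 0.45/0.75 = 0.6 times. An ICC of 0.01 then becomes 0.006, DEFF is 1.59 and the error is still about 12%. Repeat runs with 21 and with six schools per arm (1,500 each, Monte Carlo standard error about one percentage point) gave a slightly wider spread: 12–17% at 0.01, 19–27% at 0.02, 32–43% at 0.05 and 44–55% at 0.09. In the same runs a school-level ANCOVA stayed at about 4–6%.

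**Does Bonferroni cure it?** Assume six pairwise comparisons, so the per-test level is 0.05/6 = 0.83%. At m = 100 the per-test error becomes about 6% at ICC 0.01, 13% at 0.02, 28% at 0.05 and 42% just under 0.10. These are lower in absolute terms, but further above the level intended: 7.4 times at ICC 0.01.

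**The case against.** Hierarchical modelling remains the primary method, and the fallback applies outcome by outcome only below the threshold. The threshold is numerical, stated in advance and supported by a citation. It is judged on unconditional models, which contain no treatment term. At an ICC near zero the single-level test is almost correct. Consent and attrition may leave fewer than 100 students per school, which softens the effect, as the m = 50 column shows.

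All of this stands as a limit on size. None of it makes the fallback valid, because nothing in the article restores a school term or robust variance, and a citation does not change the arithmetic at this cluster size.

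Several stronger readings are tempting and should be resisted:
- A reader might infer a fixed inflation, say 3- to 10-fold. At m = 100 that range corresponds to ICCs of about 0.009 to 0.075, which the article does not give. The rule also covers smaller and larger values.
- A reader might infer that the whole trial will be analysed as if students were independent. The article does not show how many outcomes would fall below the threshold.
- A reader might see selection on the result. The trigger does not look at the treatment effect, so that charge is not supported.
- A reader might add that ANCOVA discards students with partial follow-up. The article states no missing-data method, and that is commonly left to the analysis plan.

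**Conclusion.** The concern holds and should be fixed before analysis. The article states a decision rule that, if followed, gives standard errors that are too small for a cluster-randomised comparison. This is a rule fixed wrongly, not a detail left to another document.

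Its size depends on an ICC that the article does not state. Over everything below the threshold, at m = 100 and an unadjusted two-sided 5% level, type I error runs from close to nominal to about 55%, or about 1 to 11 times. At m = 50 the upper end is about 42%. The ANCOVA that the plan names does somewhat better if school effects are stable over time, but it is not protected. Whether any reported result would in fact be false cannot be judged from the article. The ambiguity in the State-or-school trigger is a separate flaw in the same sentence and could extend the fallback to outcomes with school variance above 10%.

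**What to change.** Delete the 10% rule and the single-level ANCOVA fallback. State instead that:
- every outcome analysis keeps a random effect for school, and one for student where measures are repeated, whatever the estimated ICC;
- tests and intervals use small-sample degrees of freedom, above all for within-State comparisons with six schools per arm;
- if a model does not converge, the replacement is a school-level summary analysis, or cluster-robust standard errors with a small-sample correction.

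Deleting the rule also removes the unclear trigger. The change is one of wording only and needs no further schools, students or data. The price is wider confidence intervals for outcomes with a low ICC, which reflect the true uncertainty.
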